## Data analysis and management

### Statistical analysis

Descriptive statistics for sociodemographic variables and clinical variables will be presented. Data will be presented as mean and standard deviation. The feasibility outcomes will be presented as percentage. The SNAP scores between the intervention group and the active control group in week 4 and week 8 will be compared using a linear mixed-effects model. Other analyses include using a linear mixed-effects model to compare the SNAP (for measuring ADHD symptoms), PAS (for measuring anxiety), CSHQ (for measuring sleep disturbance), and PSS (for measuring parental stress) in the intervention group with the control group at all assessment time points. To estimate the changes with time in each group, the repeated measures ANOVA will be used. The effect sizes will be estimated using between-group mean difference divided by a pooled standard deviation.

The analyses will be based on the intention-to-treat approach. Completer analysis will be a secondary analysis. Completer is defined as those who have attended all lessons, practiced the pediatric *tuina* or parent-child interaction training at least 3 times per week during the treatment period, and completed assessment time point. As the sample size is underpowered, all analysis will be presented with 95% confidence intervals to inform the precision of the results. Since data at the pilot stage is preliminary, it should be treated with caution.

All qualitative data, including interview transcriptions, text from self-report questionnaires, and content of parent logbooks, will be analyzed using thematic content analysis, facilitated by NVivo (QSR, Melbourne, VIC). Adaptations and rationale behind all reported changes to the intervention will also be listed, analyzed, and summarized. All interviews will be audio-recorded and transcribed verbatim. The transcripts will be verified for accuracy against the sound files and revisions will be made as appropriate. Any identifiable remarks will be anonymized before transcripts being imported into NVivo.

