### Participant timelines

The treatment period will be 8 weeks. Outcomes will be measured at 3 time points: baseline, week 4, and week 8. A CONsolidated Standards of Reporting Trials (CONSORT) flow diagram demonstrates the procedure of the trial, including the recruitment, allocation, and intervention (Fig. 2). A Standard Protocol Items: Recommendations for Interventional Trials (SPIRIT) diagram shows the schedule of enrollment, intervention, and assessment (Table 1).

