### Sample size

There are few published guidance concerning how large the sample size a pilot study should be. “Rule of 12” for continuous variables recommends that at least 12 participants for pilot studies with the primary focus of estimating average values and variability for planning larger subsequent studies. This size is practical for most early-stage researchers within a single center while still providing valued preliminary information [36]. It has been proposed that a sample size ranged from 10 to 40 each group is sufficient to assess the adequacy in providing a precise estimate of the between-group effect size. Assuming a 25% dropout rate, the total sample size will be 60 (*n* = 30 in the intervention group, *n* = 30 in the active control group). A sample size of at least 30 participants in each group will help to yield a confidence interval whose lower limits can help define the range of plausible values for subsequent power analysis [37]. Such a sample size is considered to be sufficient to provide the preliminary data required to test the feasibility, acceptability, and effects of parent-administered pediatric *tuina* for preschool children and assess the study design to provide instructive information and guidance to the further fully power study.

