### Sequence generation and allocation

Children with their parents will be randomly divided into the intervention group or the active control group after the completion of baseline assessments. Block randomization will be carried out using MS Excel with a random block size of 4 to 8 at a 1:1 ratio. The allocation code will be enclosed in sequentially numbered opaque envelopes and kept by a coordinator and will dispense a code to each participant upon confirmation of completion of baseline assessment by the research coordinator. The research coordinator will be blind to the study arms, and the PI will not be involved in the post-baseline data collection.

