#### Primary outcome measure

##### Swanson, Nolan, and Pelham parent rating scale (SNAP-IV-P)

The SNAP-IV Chinese Version ADHD Scale for parents is the primary outcome measure in this study. It has 26 items that include 18 ADHD symptoms (nine inattentive, nine hyperactive/impulsive) specified in the DSM-5. Items are rated for frequency by the parents on a 4-point scale (0 “not at all” to 3 “very much”) and average ratings per item are then calculated for each subscale. The Chinese version shows satisfying test-retest reliability (intraclass correlation = 0.59), internal consistency (*α* = 0.88), concurrent validity (Pearson correlations = 0.56), and discriminant validity [38].

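### The mixed-model plan compares the arms at baseline as well as at follow-up and names no between-arm estimate that uses the baseline score, which costs precision

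*Protocol article*

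**What the plan says.** The relevant text is in the Statistical analysis section of the protocol article.

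- **First mixed-model statement, SNAP only:** scores in the two arms "in week 4 and week 8 will be compared using a linear mixed-effects model".
- **Second statement, introduced as other analyses:** SNAP, PAS, CSHQ and PSS are compared "in the intervention group with the control group at all assessment time points". Participant timelines defines the visits: "Outcomes will be measured at 3 time points: baseline, week 4, and week 8".
- **Change over time:** assigned to a repeated-measures ANOVA within each group.
- **Effect size:** "The effect sizes will be estimated using between-group mean difference divided by a pooled standard deviation". No visit is given for the SD, and the difference is not tied to the model.
- **Reporting:** "all analysis will be presented with 95% confidence intervals to inform the precision of the results".

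Sequence generation and allocation says that pairs are "randomly divided into the intervention group or the active control group after the completion of baseline assessments". The article does not list the fixed effects, say whether baseline is a covariate or a response, or say which contrast is the treatment estimate.

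**The concern.** Baseline is measured before allocation, so a difference between the arms at that visit is chance by construction. Comparing the arms there answers no question about treatment.

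The comparison also restricts the model. To report an arm difference at baseline, the model must let the two baseline means differ. Once it does, with complete data, its week-8 contrast is the plain difference in week-8 means, and the baseline score adds nothing. The only analysis that the article assigns to change over time is within-group, so it does not fill the gap.

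What is at stake is interval width. The Statistical analysis section concedes that the sample is underpowered and relies on confidence intervals. The Sample size section says that the lower confidence limit will help to set plausible values for the later power calculation. Feasibility is the primary aim and preliminary effects are the last objective listed, but those effect intervals are still meant to feed the main trial.

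**Working it through.** **The plan's own figure.** "Assuming a 25% dropout rate, the total sample size will be 60". This is a rule-of-thumb size, so there is no power calculation to reproduce. The dropout arithmetic gives 60 × 0.75 = 45 children, or 22.5 per arm.

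**Inputs.**
- n = 30 per arm at full enrolment, or 22.5 after dropout (Sample size).
- Correlation ρ between baseline and week 8: not given. An assumed range of 0.3 to 0.8 is shown.
- Stand-ins for ρ: SNAP "test-retest reliability (intraclass correlation = 0.59", and PAS test-retest coefficient 0.70 (section on the PAS). Both come from validation work and are not correlations over eight weeks of treatment.
- SNAP entry cutoff (Inclusion criteria): its position in SD units is not given. +0.5 to +1.5 SD is assumed.

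**Step 1: relative variance of the week-8 arm difference.** With equal variances at the two visits:
- week 8 alone: 1
- adjusted for baseline: 1 − ρ²
- interval width, adjusted over unadjusted: √(1 − ρ²)

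| ρ | 1 − ρ² | width ratio | unadjusted N that matches 60 adjusted = 60/(1 − ρ²) |
|---|---|---|---|
| 0.30 | 0.910 | 0.954 | 66 |
| 0.50 | 0.750 | 0.866 | 80 |
| 0.59 | 0.652 | 0.807 | 92 |
| 0.70 | 0.510 | 0.714 | 118 |
| 0.80 | 0.360 | 0.600 | 167 |

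**Step 2: 95% half-width in SD units**, t × √(2/n) × √(variance factor).
- 30 per arm, unadjusted: 2.002 × 0.258 = 0.517. Adjusted: 0.493 (ρ = 0.3), 0.417 (0.59), 0.369 (0.70), 0.310 (0.8).
- 22.5 per arm, unadjusted: 2.017 × 0.298 = 0.601. Adjusted at ρ = 0.59: 0.486.

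**Step 3: does putting baseline in the mixed model already recover this?** Simulation with 300 runs, 30 per arm, three visits, compound symmetry, ρ = 0.59 and no true effect. SE of the week-8 effect in SD units:

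| Model and contrast | SE |
|---|---|
| Weeks 4 and 8 only, baseline ignored | 0.248 |
| Baseline as a response, arms free to differ there, week-8 contrast | 0.248 |
| Same model, arm-by-time contrast | 0.235 |
| Baseline as a response, common baseline mean | 0.204 |
| Baseline as a covariate | 0.205 |

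All five estimates averaged −0.01 to −0.02, so none shows bias. The second row corresponds to a visit-wise comparison at all time points, and it matches the row that ignores baseline.

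**Step 4: SNAP after selection on SNAP.** The entry cutoff truncates the baseline distribution and lowers the correlation. For a standard normal cut at c, λ = φ(c)/(1 − Φ(c)) and the retained variance is v = 1 + cλ − λ². Week-8 variance is then f = 0.59²v + 1 − 0.59², and r = 0.59√(v/f).

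| c | v | f | r | √(1 − r²) | narrower by |
|---|---|---|---|---|---|
| +0.5 | 0.269 | 0.745 | 0.35 | 0.935 | 6% |
| +1.0 | 0.199 | 0.721 | 0.31 | 0.951 | 5% |
| +1.5 | 0.150 | 0.704 | 0.27 | 0.962 | 4% |

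PAS is not an entry criterion, so this truncation is not applied to it: √(1 − 0.70²) = 0.714, about 29% narrower.

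**The case against.** The strongest reply is that the article is condensed and silent on model terms. It neither states nor rules out baseline adjustment, and covariates are commonly left to a fuller plan. The first SNAP statement covers weeks 4 and 8 only, so baseline could be a covariate there. This stands: a reader might infer that the lead SNAP comparison is unadjusted, but that inference rests on silence.

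A second reply is that a mixed model over all visits does use baseline as a response, and with a common baseline mean it matches covariate adjustment (0.204 against 0.205). That is true of the constrained model. But a model that sets the arms equal at baseline cannot also compare them there, and the second statement includes that visit in the comparison. Read as written, it points to the unconstrained model.

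Third, on the primary scale the gain may be small, because the children are selected on SNAP. This also stands. The 19% figure and the 92-child equivalent apply to SNAP only without selection.

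Two further readings are tempting and go beyond the text. One is that four baseline significance tests are planned, with an 18.5% chance (1 − 0.95⁴) of at least one false signal if they were independent. The article speaks of comparing and of intervals, and states no baseline test or alpha. The other is that the effect size will be inflated by division by a truncated baseline SD. The article does not say which visit supplies the SD, and nothing in it points to baseline.

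**Conclusion.** The point holds for the analysis at all assessment time points. It includes a between-arm comparison before randomisation that can show only chance, and its visit-wise week-8 contrast is no more precise than one that ignores baseline. Nowhere does the article name a between-arm estimate that uses the baseline score.

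This is a loss of precision. A reader might take it as bias, but randomisation keeps every one of these contrasts unbiased, and the simulation agrees.

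The size rests on assumptions. Across the assumed correlations, intervals would be about 5% to 40% narrower with adjustment. The scale-specific figures borrow test-retest coefficients, and the SNAP figure also needs an assumed cutoff position and a normal score distribution. On those terms the gain is appreciable for PAS and modest for SNAP. The article gives no test-retest figure labelled as such for CSHQ or PSS, so only the general range applies to them. The change should be made because it is free and the intervals are meant to inform the main trial.

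**What to change.** For each scale, replace the two mixed-model statements with one:

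- Fit a mixed model to the week-4 and week-8 scores with arm, visit, arm × visit and the baseline score as covariate. A model with baseline as a response and a common baseline mean for the two arms is an equivalent choice.
- Limit the between-arm contrasts to weeks 4 and 8, each with its 95% interval.
- Report baseline by arm descriptively only.
- Define the effect size as the adjusted week-8 difference divided by the pooled week-8 SD.

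If a fuller protocol or analysis plan already specifies such a model, bring the sentence on all assessment time points into line with it. The cost is wording only: the baseline scores are already collected, and no new data are needed.

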### Eligibility criteria

#### Inclusion criteria

Inclusion criteria for the children are the following:
Children between 3-7 years old by the start of the assessmentHaving a score equal to or higher than the borderline cutoff of the Swanson, Nolan, and Pelham Parent Rating Scale (SNAP) [38], indicating the children had moderate ADHD symptoms

Children with ADHD symptoms of hyperactivity, anxiety, or sleep disturbance will be recruited in this study. We will not restrict the children to have a formal medical certificate since children are usually assessed and diagnosed by professionals after 7 years old; hence, their hyperactivity, anxiety, and sleep disturbance symptoms have not yet received a diagnosis. We will consider these children according to the inclusion criteria.

Inclusion criteria for parents are the following:
Able to communicate using MandarinWilling to learn the knowledge and manipulations of pediatric *tuina* for ADHD symptomsAvailable to take their children to the designated hospital for pattern identification and conduct manipulations at home according to the study processAgree to give informed consent

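### Within-group change by repeated-measures ANOVA, in its classical form, drops children with a missed visit; take descriptive within-arm changes from the planned mixed model instead

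*Protocol article*

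**What the plan says.** Under Statistical analysis, the article compares SNAP scores between arms with a mixed model: they "in week 4 and week 8 will be compared using a linear mixed-effects model". The same kind of model is planned for SNAP, PAS, CSHQ and PSS at all assessment times. For change within an arm the method switches: "To estimate the changes with time in each group, the repeated measures ANOVA will be used". The next paragraph sets the population for the analyses without exception, "The analyses will be based on the intention-to-treat approach", and then adds "Completer analysis will be a secondary analysis". Effect sizes are defined between groups, results carry 95% confidence intervals, and the text asks for caution with pilot data.

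Four other places bear on the point:
- Participant timelines: "Outcomes will be measured at 3 time points: baseline, week 4, and week 8".
- Sample size: "Assuming a 25% dropout rate, the total sample size will be 60", with 30 per arm.
- Inclusion criteria: a child must have "a score equal to or higher than the borderline cutoff of the" SNAP parent scale. No numerical cutoff is printed.
- SNAP-IV-P section: the same scale is the primary outcome measure, with "test-retest reliability (intraclass correlation = 0.59").

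**The concern.** There are two separate issues.

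**Sample.** Classical repeated-measures ANOVA needs a full row of data for each child. A child who misses week 4 or week 8 leaves the analysis entirely, including the scores already collected. The mixed model keeps partial records. The within-arm and between-arm results in one paper would then rest on different children and could disagree for that reason alone. Loss may also be selective. Under Withdrawal criteria, starting another therapy for ADHD symptoms is a reason for withdrawal, and those children are plausibly the ones not improving. If they lack later scores, a complete-case change would tend to look too favourable.

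**Interpretation.** Change from baseline within one arm mixes treatment with natural course, usual care and the expectations of unblinded parents, who both deliver the intervention and rate the outcome. Selection on a high score of a scale with moderate reliability may add regression to the mean. A clear fall in each arm could then be taken for a preliminary effect of tuina.

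**Working it through.** **1. Children in the ANOVA.** Inputs: 60 children, 30 per arm, 25% dropout (Sample size) and three visits (Participant timelines).

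The article gives no sample size before inflation, so 60 cannot be derived forward. Working backward, 60 × (1 − 0.25) = 45, and 45 / 0.75 = 60. Per arm, 30 × 0.75 = 22.5. If each dropout lacks at least one later score, classical ANOVA keeps about 22 to 23 of 30 per arm and discards 7 to 8, or 15 of 60 overall.

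If scores are instead missed independently at weeks 4 and 8 with an assumed rate m per visit, the number kept is 30 × (1 − m)²:

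| m (assumed) | Kept per arm |
|---|---|
| 5% | 30 × 0.95² = 27.1 |
| 10% | 30 × 0.90² = 24.3 |
| 15% | 30 × 0.85² = 21.7 |

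**2. Regression to the mean, if the qualifying SNAP is also the baseline.** Input from the article: ICC 0.59. Assumptions not in the article: normal scores, independent errors, and a cutoff c in SDs above the mean of the source population. With no treatment effect,

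expected fall = (1 − ICC) × φ(c) / (1 − Φ(c)), in population SDs.

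| c (assumed) | φ(c)/(1 − Φ(c)) | Expected fall, × 0.41 |
|---|---|---|
| 0 | 0.798 | 0.33 SD |
| 0.5 | 1.141 | 0.47 SD |
| 1.0 | 1.525 | 0.63 SD |
| 1.5 | 1.939 | 0.79 SD |

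**3. How often the ANOVA would show a significant fall with no effect.** Simulation of 1,500 trials per setting, three visits, 30 per arm, assumed 5% level, qualifying score reused as baseline:

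| Reliability | Cutoff 0 / 1 / 1.5 SD: one arm | Both arms |
|---|---|---|
| 0.59 (article) | 0.56 / 0.99 / 1.00 | 0.29 / 0.98 / 1.00 |
| 0.8 (assumed) | 0.27 / 0.79 / 0.95 | 0.08 / 0.62 / 0.91 |
| 0.9 (assumed) | 0.15 / 0.46 / 0.68 | 0.03 / 0.22 / 0.47 |

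With 22 per arm, ICC 0.59 and a 1 SD cutoff, the rates are 0.96 for one arm and 0.91 for both.

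**4. The same simulation with a fresh baseline SNAP after screening.** With independent errors the expected later fall is zero. A significant improvement appears in one arm in about 2% to 3% of trials, and in both arms in almost none.

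**5. The between-arm contrast.** Its false-positive rate stays at about 4% to 6% in every setting, because randomisation follows the baseline assessment and both arms regress equally in expectation.

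**The case against.** The strongest reply has four parts.

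**The article specifies no case deletion.** The ANOVA could be run on imputed data, and missing-data handling is commonly left to an analysis plan that is not shown. This stands in part: deletion is a property of the classical method, not a stated rule. But the method itself is stated, so the point does not rest on silence. It is also fair that a child with a baseline score only adds little to a mixed-model estimate of change. The gain comes mainly from children with one later score, so losing 7 to 8 children per arm overstates the lost information on change.

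**A reader might infer that both arms are bound to show improvement from regression to the mean alone.** The documents do not support that. The article describes screening first, then a baseline assessment scheduled for eligible participants, then randomisation. It does not say that the qualifying SNAP is reused, and step 4 shows that the problem vanishes under a fresh baseline with independent errors. The cutoff's distance from the source mean is also unknown. The selection argument applies directly to SNAP only; PAS, CSHQ and PSS have no entry cutoff.

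**A reader might infer that the mixed model cures both faults.** It does not. Regression to the mean comes from selection, and within-arm contrasts carry it whatever model produces them.

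**The article does not say that within-arm change will be read as efficacy.** This stands. The effect objective is comparative, effect sizes are between-group, and caution is already urged. The ANOVA is ancillary in a feasibility pilot.

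**Conclusion.** The method is poorly chosen, with limited consequence. In its classical form the ANOVA would use about 22 to 23 of 30 children per arm, provided that the 25% dropout means missing scores and no imputation is used. That is in tension with the intention-to-treat statement and inconsistent with the mixed model beside it.

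The regression-to-the-mean risk on SNAP is conditional. If the qualifying score is the baseline, the fall is roughly 0.3 to 0.8 SD for assumed cutoffs of 0 to +1.5 SD. With a fresh baseline and independent errors it is about zero. The between-group comparison is not biased by it in either case. The point is minor to moderate: a free improvement.

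**What to change.** Replace the ANOVA sentence under Statistical analysis with wording such as: *Changes from baseline to weeks 4 and 8 within each arm will be estimated as contrasts from the same linear mixed-effects model, with 95% confidence intervals. They are descriptive, and no within-arm p-values will be reported. Statements about effect will rest on the between-arm difference.*

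Also say in one clause whether the SNAP score used for eligibility is the baseline score, so that readers can judge how far within-arm change on SNAP may reflect regression to the mean.

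The cost is a sentence or two of text. No data are added, and there is one analysis fewer to run.

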### Date management

Data will be collected through e-questionnaires, which will be kept strictly confidential, and could only be used for purposes related to this study. Data collected will be stored in our data system for 3 years and destroyed after that. Participants have the right to use their personal data, such as inspection, preservation, management, disclosure/non-disclosure, erasure, and/or in any way dealing with or disposing of any of their personal data in or for this study.

## Discussion

This pilot trial aims to assess the feasibility of parent-administered pediatric *tuina* for ADHD symptoms in preschool children. There have been several studies conducted on pediatric *tuina* for ADHD; however, those studies were limited by various methodological problems such as invalidated outcomes measures, unclear randomization and allocation concealment methods, lack of appropriate control intervention to test the specific effects. To more rigorously assess the preliminary effects of pediatric *tuina*, we designed this pilot trial to overcome the limitations of previous studies.

Children in the intervention group will receive individualized *tuina* prescriptions. It might increase the complexity of the intervention and hamper the reproducibility of the intervention, but treatment individualized based on TCM pattern identification is believed to be the optimal practice of pediatric *tuina*. Our design will simulate the real-world practice of *tuina* in the clinical setting.

The pediatric *tuina* is a complex intervention based on TCM theory and past clinical experience, of which the theoretical framework is relatively less researched. Therefore, we included a process evaluation and proposed a logic model to depict the possible causal assumption and mechanism of impacts of pediatric *tuina*. This logic model will inform further fully-powered study and guide trials with similar parent-administered settings in future research.

We use parent-child interaction training as a control intervention which includes the progressive muscle relaxation exercise and health educational materials. The use of sham acupressure as a control intervention is difficult as the non-acupoint locations are not well defined [50]. This control design offers training on muscle relaxation and coping skills, and education of ADHD knowledge to the parents. Both groups contain components that aim to improve parent-child interaction, relive children’s ADHD symptoms, and enhance parents’ knowledge of ADHD. This controls the non-specific effects of pediatric *tuina* due to enhanced parent-child interactions and contacts time to the research personnel.

We anticipate that there will be a few practical issues in performing this study. Firstly, the subjects will be provided with two consultations for TCM pattern identification (one at baseline and one at the end of first month) and the *tuina* prescription may be adjusted. However, the subjects may be more preferable to the original manipulation that they learned at the beginning as they have already mastered the manipulation and found benefit effects. In this case, we may offer them an option to continue the original manipulation. Secondly, parents usually have a great commitment to their family and their time schedule may be less flexible. Although we will inform them the schedule of the training lessons before baseline assessment, we foresee that some parents may not be able to attend all the lessons after randomization.

There are several limitations to this pilot study. First, given the nature of the intervention and the control intervention, it is impossible to blind either the parents, children, or TCM practitioners. To minimize the detection bias, the TCM practitioners would not be involved in the outcome assessment and the outcome assessors will be blinded during the process of intervention conduction and data collection. Second, although we will use MoCA to ensure that the parents have a normal cognitive function, the discrepancies in the learning abilities and education level may affect their mastery of the *tuina* technique and hence the effects of the treatment. However, it would truly reflect the implementation of the intervention in the daily clinical practice as the parents’ backgrounds usually vary. Finally, our control group did not test the *tuina’s* specific effect of exerting physical pressure on the specific body location based on meridian theory.

Our study will add to the current evidence of pediatric *tuina* for ADHD in preschool children based on meridian theory. Parent-administered pediatric *tuina* is a potential alternative therapy with fewer side effects and economic burden, and is more flexible for parents and children to receive the treatment. Our results will also inform the clinicians and practitioners about the feasibly of training the parents to administer the *tuina* technique to relieve their child’s ADHD symptoms.

